## Abstract

**Background:**

A considerable percentage of flight crew reports to be fatigued regularly. This is partly caused by irregular and long working hours and the crossing of time zones. It has been shown that persistent fatigue can lead to health problems, impaired performance during work, and a decreased work-private life balance. It is hypothesized that an intervention consisting of tailored advice regarding exposure to daylight, optimising sleep, physical activity, and nutrition will lead to a reduction of fatigue in airline pilots compared to a control group, which receives a minimal intervention with standard available information.

**Methods/design:**

The study population will consist of pilots of a large airline company. All pilots who posses a smartphone or tablet, and who are not on sick leave for more than four weeks at the moment of recruitment, will be eligible for participation.

In a two-armed randomised controlled trial, participants will be allocated to an intervention group that will receive the tailored advice to optimise exposure to daylight, sleep, physical activity and nutrition, and a control group that will receive standard available information. The intervention will be applied using a smartphone application and a website, and will be tailored on flight- and participant-specific characteristics. The primary outcome of the study is perceived fatigue. Secondary outcomes are need for recovery, duration and quality of sleep, dietary and physical activity behaviours, work-private life balance, general health, and sickness absence. A process evaluation will be conducted as well. Outcomes will be measured at baseline and at three and six months after baseline.

**Discussion:**

This paper describes the development of an intervention for airline pilots, consisting of tailored advice (on exposure to daylight and sleep-, physical activity, and nutrition) applied into a smartphone application. Further, the paper describes the design of the randomised controlled trial evaluating the effect of the intervention on fatigue, health and sickness absence. If proven effective, the intervention can be applied as a new and practical tool in fatigue management. Results are expected at the end of 2013.

**Trial registration:**

Netherlands Trial Register: NTR2722

## Background

Long and irregular working hours as well as crossing multiple time zones are common working conditions of flight crew [1]. These conditions can cause travel fatigue, reduce sleep quality and quantity, and disrupt the circadian rhythm. The latter can lead to jet lag symptoms as well [1,2]. All factors may contribute to increased fatigue. Prolonged fatigue has been shown to cause health problems, impaired performance capability and a disturbed work-private life balance [3]. Furthermore, it has become clear that long term exposure to reduced sleep and circadian disruption can lead to cardiovascular diseases, gastrointestinal disorders, and cancer [4-6]. More recently, this exposure has also been related to body weight gain, metabolic syndrome, and diabetes [7-9].

Among flight crew, fatigue is experienced regularly [10]. In a study conducted in New Zealand for instance, 64% of the participating pilots reported to be fatigued at least once a week due to their working hours [11]. In comparison, in a Dutch cohort study of a general working population, the prevalence of fatigue due to work was found to be 22%. Another study among pilots showed that 75% of them acknowledged fatigue as a serious problem during their job. Further, 71% of them admit to have been dozed off at least once during a flight [1].

In recent years, more knowledge has become available about the influencing factors on disturbance of the circadian rhythm, and possible countermeasures of fatigue [12-14]. It has been shown that by correct timing of exposure to and avoidance of daylight, the most important biorhythm synchronizer (or zeitgeber) [2,12,13], jet lag symptoms can be reduced. Additionally, an optimal timing and duration of sleep can reduce the disturbance of the biological clock and thereby, reduce fatigue [2,13,14]. Further, correct timing of certain types of physical activity can enhance sleep duration and quality [3]. Moreover, the intake or avoidance of food may diminish jet lag symptoms during certain phases of the sleep/wake cycle, and caffeine can temporarily alleviate fatigue [3,12-14]. Additionally, the specific macronutrient composition of meals has shown to be able to stimulate either alertness or relaxation [15,16]. Based on these findings, several measures have been proposed to counter the negative effects of the aforementioned working conditions of flight crew.

These general measures should be translated into practical advice to enhance implementation. For flight crew, the specific advice depends on several variables (e.g. flight direction, flight duration, and number of time zones crossed). This implies that the advice differs per destination and person (e.g. morning vs. evening types), and that the total number of different advices is high. Due to this complexity, translating the theoretical knowledge into training programs for flight crew has proven to be difficult [2,17]. Airlines and authorities sometimes provide employees with fatigue-related information at the start of their job, but most often continued education is not assured. And although aircraft companies such as Boeing and Airbus developed training modules aiming to reduce fatigue, the effects of these programs have hardly been examined systematically [17,18]. The few studies that did study the effects of such training programs, reported some effects [19,20] but they combined their training programs with alterations in work schedules, so that it was impossible to address the measured fatigue reduction and performance improvement to the training program alone. Other studies did find improved knowledge, awareness [21], layover sleep, and in-flight alertness [22] after short term application of fatigue management advice in flight crew, but did not measure the long term effects.

Further, in the aforementioned studies, advice was mostly transferred through the use of paper or in the form of books or instruction materials. This kind of implementation has led to low compliance, which was shown in an article by Flower [23]. Their advice cards program among British Airways pilots was received positively, but the compliance of 40% proved to be low. Therefore, it might be possible that the lack of compliance and outcomes in transferring fatigue-related knowledge to flight crew is (partly) due to the chosen medium. There might be a solution for this implementation problem because in more recent health behaviour literature, the large potential of the use of new media sources, such as computers and internet, has become clear [24,25]. It has been stated that the use of web-based interventions is more effective in increasing health behaviour knowledge compared to non-web-based interventions [26]. Further, to improve adherence, these interventions should be designed to allow individuals to tailor it to their own specific needs. This so called tailoring can significantly affect behaviour regarding safety, smoking, physical activity and dietary intake [24,27,28].

In summary, it can be stated that it is still largely unclear what the effects are of tailored advice regarding exposure to daylight, sleep, physical activity, and nutrition on fatigue of flight crew. Therefore, this paper describes the development of an intervention consisting of tailored advice for airline pilots, and the design of the randomised controlled trial evaluating the effect of the intervention on fatigue, health and sickness absence. The advices are evidence-based and aim to optimise the pilots’ behaviour with regard to:

•Exposure to daylight (timing and duration)

•Sleep (sleep behaviour and timing of sleep)

•Nutrition (dietary behaviour and timing of dietary behaviour)

•Physical activity (form and timing of physical activity)

It is hypothesized that an intervention consisting of easy obtainable tailored advice, will lead to a significant reduction of fatigue in airline pilots compared to a minimal intervention, based on standard fatigue related information available within the airline company.

## Methods/design

An intervention has been developed and will be evaluated by means of a two-armed randomised controlled trial (RCT). The intervention, named MORE Energy, will have a follow-up period of six months. The recruitment of the participants will start in autumn 2012. The study design and procedures have been assessed by the Medical Ethics Committee of the VU University Medical Center, Amsterdam, the Netherlands (#2011/065).

### Study population

The study population will consist of pilots of all aircraft types of a large internationally operating airline company.

### Study procedures

The study design is presented in Figure 1. First, potential participants will be made aware of the project by means of a publicity campaign, using intranet, internet and news bulletins. In addition, meetings with supervisors will be held to make sure they can propagate the study to their employees, and motivate them to participate.

**Figure 1 F1:**
[figure not shown]
Study design.

After the publicity campaign, all pilots will receive a postal information brochure. In this brochure, the pilots will be made aware of the participation mail, which they will receive in their company e-mail inbox. In this e-mail, all potential participants will be asked to fill in the baseline questionnaire, by using the included unique internet link. By filling in the questionnaire the pilots agree to participate in the study, no additional written informed consent will be obtained. After the researchers receive the filled in questionnaire, participants will be allocated to either the control or intervention group.

### Inclusion and exclusion criteria

The pilots can participate in the study if they:

•are not on sick leave for more than four weeks at the moment of recruitment;

•own a smartphone or tablet with an Android or iOS (iPhone/iPad) operating system.

### Randomisation

Study group allocation will be conducted at individual level, using the minimisation technique. After the baseline measurement the participants will be assigned to one of the two study groups. A minimisation procedure will make sure that the group allocation of the next participant enrolled in the trial takes into account the characteristics of those participants already enrolled. The aim is that each allocation should minimise the imbalance across multiple factors [29]. The factors that are considered for minimisation are aircraft type (five different types of aircraft units), and job title (captain, first officer, and second officer).

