### Statistical analysis

To investigate the success of the randomisation procedure, potential confounders or effect modifiers (age, gender, type of aircraft flown, household composition, morningness-eveningness) will be compared between the intervention and control group by Student t-tests for independent samples and Chi square tests (χ2).

The effectiveness of the intervention (time*group interaction) will be analysed using linear mixed model analyses with the outcome measures at follow-up (T1-T2) as the dependent variables. The dependent variables are fatigue, sleep, physical activity, nutrition, need for recovery, sickness absence, work-private life balance, general health and knowledge, whereas research condition (intervention or control group) is the independent variable. Possible confounding or mediating factors will be considered.

A detailed analysis plan will be developed prior to finalisation of the dataset. For all analyses a two-tailed significance level of <0.05 will be considered statistically significant. The analyses will be performed using PASW 20.0 (SPSS Inc. Chicago, Illinois, USA).

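### Allocation is minimised on aircraft type and job title, but the analysis section commits neither to the effect model and its stated route for choosing covariates would tend to drop both

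*Protocol article*

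**What the plan says.** All references are to the protocol article.

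- **Randomisation.** "Study group allocation will be conducted at individual level, using the minimisation technique". On the factors: "The factors that are considered for minimisation are aircraft type (five different types of aircraft units), and job title", the latter with three ranks.
- **Statistical analysis, effect model.** Effectiveness, described as a time-by-group interaction, "will be analysed using linear mixed model analyses with the outcome measures at follow-up (T1-T2) as the dependent variables". On the model terms: "whereas research condition (intervention or control group) is the independent variable. Possible confounding or mediating factors will be considered".
- **Statistical analysis, baseline check.** To judge how well randomisation worked, "potential confounders or effect modifiers (age, gender, type of aircraft flown, household composition, morningness-eveningness) will be compared between the intervention and control group", using t-tests and chi-square tests. Aircraft type is on this list; job title is not.
- **Other study parameters.** Job title and flight unit are both recorded at baseline.
- **Statistical analysis, deferral.** A detailed analysis plan is to be written before the dataset is final.

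**The concern.** Two parts of the article do not meet. The allocation is built on two factors, yet the analysis section makes neither a committed model term, and one of them, job title, is not mentioned there at all.

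The only route into the model that the section states for other variables is as confounders or mediators. Minimisation makes the arms nearly equal on its own factors, so these will rarely look imbalanced and will barely move the treatment estimate. A choice of covariates based on confounding would therefore tend to reject exactly the variables that the allocation used. The reason to adjust for them is the allocation method, and the section does not give that reason.

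The standard error is at stake. A model without the factors counts their contribution to fatigue as random error that could differ between arms, although the design has largely removed that difference. The estimate then varies less than the model reports, so intervals are too wide and p-values too large, to the extent that the factors predict fatigue.

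**Working it through.** **Inputs.** From Sample size: SD 19.8, mean 47.3, 246 per group, power 0.80, alpha 0.05, loss to follow-up 25%, total 656. From Statistical analysis: two-sided test. From Randomisation: five aircraft units and three job titles. *Assumption:* R2, the share of CIS variance explained by the two factors beyond any other model terms, is not in the documents; a range of 0 to 0.20 is shown.

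**The plan's own figure.** n per group = 2 × SD² × (1.960 + 0.842)² / d².

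- With d = 10% of 47.3 = 4.73, n = 276, which is not 246.
- The difference that 246 per group detects is d = 19.8 × 2.802 × √(2/246) = 5.00 points.
- The total reproduces: 492 / 0.75 = 656.

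I use d = 5, at which 246 per group gives 80.0% power. At 4.73 points power is already 75.5% with R2 = 0. That shortfall is a separate sample-size matter and does not come from the covariates.

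**Effect of leaving the factors out, assuming near-exact balance.**

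- Model SE = 19.8 × √(2/246) = 1.785.
- True SE = 1.785 × √(1 − R2).
- SE excess = 1/√(1 − R2) − 1.
- True size = 2 × [1 − Φ(1.960/√(1 − R2))].
- Unadjusted power = Φ[(5 − 1.960 × 1.785) / (1.785 × √(1 − R2))].
- Adjusted power = Φ[5 / (1.785 × √(1 − R2)) − 1.960].

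Example, R2 = 0.05: true SE = 1.785 × 0.975 = 1.740. Unadjusted power = Φ(1.501/1.740) = Φ(0.862) = 80.6%. Adjusted power = Φ(2.873 − 1.960) = Φ(0.913) = 82.0%.

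| Assumed R2 | SE too large by | True size of 5% test | Power, unadjusted | Power, adjusted | Points forgone |
|---|---|---|---|---|---|
| 0 | 0% | 5.0% | 80.0% | 80.0% | 0 |
| 0.02 | 1.0% | 4.8% | 80.2% | 80.8% | 0.6 |
| 0.05 | 2.6% | 4.4% | 80.6% | 82.0% | 1.4 |
| 0.10 | 5.4% | 3.9% | 81.2% | 83.9% | 2.7 |
| 0.20 | 11.8% | 2.8% | 82.6% | 87.9% | 5.3 |

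(Points forgone are taken from unrounded powers.)

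**Check by simulation.** Minimisation of 492 pilots over 5 × 3 factor levels was simulated with 3,000 runs per R2, one follow-up score and a linear model. The biased-coin probability of 0.8 and the rank shares of 45/40/15% are assumptions.

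- R2 = 0: sizes and powers of the two models agree (size 4.8% in both; power 79.1% and 79.3%).
- R2 = 0.05: unadjusted size 4.1%; power 80.8% unadjusted, 82.0% adjusted.
- R2 = 0.10: unadjusted size 4.2%; power 80.0% and 82.8%.
- R2 = 0.20: unadjusted model SE 1.78 against an empirical 1.55; size 2.5%; power 83.3% and 88.1%.

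At each non-zero R2 the direction matches the formulas, and the sizes agree within what 3,000 runs can resolve.

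**The case against.** The strongest reply is that the article fixes no covariate set and so gets none wrong. The sentence naming study group identifies the exposure of interest and cannot be a full list of terms, because the time-by-group interaction in the same paragraph needs time in the model too. The list that omits job title serves a baseline comparison and is not a model specification. Details are deferred to a plan that may well add both factors. Balance is the aim that the article gives for minimisation, and balance is delivered with or without adjustment. Any error is conservative.

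Most of this stands, and it rules out several stronger readings:

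- A reader might infer that the two factors are excluded from the model. They are not: aircraft type is a named candidate and job title remains available.
- A reader might infer that the standard errors are certainly too large. That depends on an R2 that no section reports. Development of the intervention says that short-haul and long-haul pilots need different advice, which makes some link with fatigue plausible but gives no size.
- A reader might infer that power falls below the planned 80%. At 5 points the unadjusted test keeps 80.0 to 82.6%; the loss is only against the adjusted analysis.

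The reply does not remove the mismatch. The article does more than stay silent on covariates: it states a criterion, confounding or mediation, which is the wrong one for factors balanced by design, and its candidate list leaves out one of the two.

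**Conclusion.** The point holds as a modest defect in how covariates are to be chosen. Neither minimisation factor is a committed term, job title is absent from the analysis section, and selection by confounding would tend to drop both. If that happens and the factors predict fatigue, the primary interval is too wide and the test conservative. There is no bias and no inflation of false positives.

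The consequence is nil at R2 = 0 and small up to R2 = 0.05. Only towards R2 = 0.20 does it become appreciable, with a standard error 11.8% too large and about 5 power points forgone.

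These figures assume near-exact balance, equal arms (implied by the sample size), and a group comparison of follow-up scores with SD 19.8. If baseline fatigue is also in the model, the share left for the two factors to explain could be smaller, and the effect with it.

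**What to change.** State in the Statistical analysis section, and carry into the detailed analysis plan, that aircraft type (five levels) and job title (three levels) are fixed covariates in every effectiveness model because allocation was minimised on them, whatever the baseline comparisons show. Keep this separate from the sentence on confounding and mediating factors, so that no data-driven rule can remove them.

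The cost is one sentence and (5 − 1) + (3 − 1) = 6 model parameters, against 492 expected completers. No new data are needed, since both variables are already collected at baseline, and the sample size need not change on this account.

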### Development of the intervention

To optimize the content of the advices, a literature study was performed in order to gain insight in the latest scientific knowledge regarding work-related fatigue in flight crew. Based on this literature study, the following intervention objectives were defined (Figure 2).

**Figure 2 F2:**
[figure not shown]
Intervention objectives.

It is hypothesized that tailoring the relevant fatigue-related information, and making it easy accessible to the flight crew, will lead to improvement of their knowledge about the different aspects. This will be measured using knowledge tests before and during the intervention. Improved knowledge will enlarge the possibility that the participant will use this knowledge to improve their behaviour regarding exposure to daylight, sleep, physical activity and nutrition, before, during, and after flight schedules. Accordingly, it is hypothesized that if their behaviour is altered, participants’ circadian disruption and fatigue will reduce, leading to an improvement of general health.

To find out what implementation strategy and what medium should be used to optimise compliance to the intervention, focus groups with the target population were held. For each aircraft type, two focus groups were organised. Considering five different types of aircrafts, ten focus groups were held. A total of 30 pilots attended the focus groups, heterogeneous regarding age, gender and job title. The discussions were recorded and field notes were written. The focus groups made clear that the intervention should be easy available, appealing, and to be used by pilots of all ages and ranks. Further, it was made clear that the intervention should be evaluated by means of a test phase first, and that it should be evident that the advice given is evidence based. The advices should be made flight schedule specific; short haul pilots have a different need for information and advice than long haul pilots have.

The input from these meetings was used to elaborate the intervention strategy and to take into account the raised facilitators and barriers for implementation. Finally, interviews with key management stakeholders were held, aiming to match the intervention to the present laws and legislation, collective labour agreement, and the policy of the airline company.

After the development of the intervention, it was pre-tested by pilots and researchers. The group of test pilots was heterogeneous with respect to both aircraft units and job type. In total, 34 pilots were invited to take part in this test phase, which lasted eight weeks in total. At the end of this period, the pilots who had actually participated were asked to fill in a digital evaluation form. Further, they were asked if they were available for a telephone consultation, in case the researchers needed additional information from them. Based on the results of the test phase evaluation, the intervention was reconsidered and optimised where necessary. An important result of the test phase was the report of the short-haul pilots that their advice was not substantive enough. This issue was addressed by adding more extensive advices with regard to short-haul flight schedules.

### Description of the intervention

As a result of the focus groups, a tailoring strategy was constructed. It was decided that the best tool to transfer the knowledge would be using a smartphone application. This ensures that the advice can be supplied tailored to flight characteristics (e.g. flight direction, departure and return time, number of time zones crossed) and to personal characteristics (morning vs. evening types).

For each destination with its specific schedule, the participants are provided with specific advices on optimal sleep, nutrition, and physical activity, in order to reduce fatigue. The user can fill in his flight and location, after which he will receive the advices. Subsequently, the user can choose himself to read extensive information about either exposure to daylight, sleep, nutrition, or physical activity in the glossary menu. For each screen of the application, a help menu is available.

A website containing more background information was developed alongside the smartphone app. In the app, the user is guided to the website to read, listen to and see more detailed information. See Additional file 1 for examples of the application and website.

Participants in the intervention group will be stimulated to consider the advice on the application and the website by means of reminders. The first form of reminding occurs through timed alerts; the user receives an alert once he has not opened the app for longer than three weeks. Another reminder strategy that will be used is called geofencing; the user is given an alert each time he is outside the Netherlands, with a maximum of one alert per four days.

